## Abstract

The effect of probiotics in improving or maintaining oral health in orthodontic patients is understudied. The aim of this study is to evaluate the effect of probiotic administration in addition to tooth brushing on clinical gingival inflammation, plaque formation, subgingival microbiota composition, and salivary biomarkers of inflammation in adolescents with fixed orthodontic appliances. The present study is a 6-month, double-blind, two-arm, placebo-controlled, single-center trial, in which 116 adolescent volunteers aged 12–16 years will be recruited from the patients of the orthodontics clinic of the University Hospital of Lille, France. Subjects who meet the eligibility criteria will be allocated to one of the following groups: (i) control: two placebo lozenges per day for 90 days together with regular oral hygiene, (ii) test: two probiotic lozenges per day for 90 days together with regular oral hygiene. Clinical assessment and biological sample collection will be performed at baseline, 3 and 6 months. In addition, compliance outcomes and adverse events will be monitored.

## 1. Introduction

Fixed orthodontic appliances (FOA) including brackets, orthodontic bands, and wires are commonly used in orthodontic therapy to correct dental malposition. These fixed appliances, left in place for a prolonged duration, facilitate the accumulation of dental biofilm and make tooth brushing more challenging and time-consuming [1,2]. The persistence and accumulation of biofilm alter the composition of the supra- and subgingival microbiota. Thus, orthodontic patients present significant qualitative and quantitative differences in supra- and subgingival plaque compared to subjects without orthodontic appliances [3]. A recent study indicated a significant increase in *Bacteroidetes* and *Saccharibacteria* (formally TM7) and decrease in Proteobacteria and Actinobacteria over time, in both plaque and saliva [4]. At genus level, an increase in relative abundance of obligate anaerobes—including periodontal pathogens—was observed, which is likely to contribute to the increased prevalence of gingivitis during orthodontic treatment [5]. Importantly, these alterations in the composition of the oral microbiota would only be partially reversed even two years after the removal of fixed orthodontic appliances [6,7]. In this respect, supporting interventions for daily oral hygiene and oral health maintenance are needed for the favorable outcome of orthodontic treatment.

Probiotics are live organisms that confer health benefits to the host when administered in adequate amounts [8]. Since it is recognized that changes in the composition of dental biofilm play a key role in the initiation and progression of periodontal diseases, the administration of probiotic strains has been proposed to be useful in the prevention and treatment of these diseases [9,10,11,12]. *Lactobacillus* and *Bifidobacterium* are the most frequently described probiotics among which *Lactobacillus reuteri* (*L. reuteri*) is one of the most studied strains [13]. In vitro, probiotic strains can modulate the immuno-inflammatory response and are effective against oral pathogens through direct (adhesion or nutritive competitions and/or the secretion of antimicrobial molecules) and indirect (environmental modifications) mechanisms [13]. While a growing number of clinical studies have reported the use of probiotic to prevent or treat gingivitis and periodontitis, there is still a lack of clear evidence regarding their benefits [14,15,16,17,18,19].

From an ecological point of view, the origin of periodontal disease is a disruption of resilience caused by a “shift regime” (i.e., large, abrupt, persistent changes in function and structure) [20] within the normally stable resident oral microbiome [21]. The placement of fixed orthodontic appliances may lead to such changes, thus facilitating the establishment of local disease by promoting the accumulation of food debris and bacterial proliferation [1,2]. The composition of the microbiota associated with periodontal disease is complex and may include species from different phyla such as *Bacteroidetes*, *Firmicutes*, *Proteobacteria*, *Spirochaetes* and *Synergistetes and Saccharibacteria* [22]. The pathogenesis of periodontitis is also characterized by the high complexity of the immune-inflammatory mechanisms involved. A large number of signaling molecules are involved in the regulation of the host response and some are used as biomarkers of disease activity, progression, or resolution. This includes chemokines (e.g., IL-8, MIP-1, MCP-1, RANTES), cytokines (e.g., IL-1, TNF-α, INF-γ), arachidonic acid derivatives (e.g., PGE2), and proteases (e.g., matrix metalloproteinases, cathepsins) [23,24,25,26]. In this context, the use of orally active probiotics is expected to help in improving the resilience of the oral microbiome [27,28]. Probiotics produce compounds, including bacteriocins, that could contribute to the reduction of bacterial biofilms. Probiotic bacteria also prevent colonization by new pathogens by a firm adhesion to the surfaces of the oral cavity. Through this process, bacterial aggregation and co-aggregation occur, resulting in a new microbial balance and a healthy biofilm [29]. Furthermore, probiotics have been shown to modulate natural and acquired immune responses, via downregulation of inflammatory cascades by various mechanisms [30]. In vitro, the findings tend towards a modulation in the expression and/or production of IL-1β, TNFα, PGE2, TLR2-4, IL-8 and IL-10 by *Lactobacilli* and *Bifidobacteria* used in mono- or co-infection with periodontal pathogens on human gingival epithelial cells or fibroblasts [14]. Kobayashi et al. reported that oral administration of *Lactobacillus gasseri* was effective in preventing *Porphyromonas gingivalis*-induced periodontal disease in mice [31]. Data from clinical studies have shown a significant decrease in the prevalence of Gram-negative periodontal pathogens, including *Porphyromonas gingivalis*, *Aggregatibacter actinomycetemcomitans* and *Tannerella forsythia*, as well as a significant decrease in the level of proinflammatory cytokines in gingival crevicular fluid, after repeated consumption of probiotic *Lactobacillus* species [32,33,34]. Shimauchi et al. reported a decrease in the amount of biofilm on dental surfaces (reduction in plaque index) and an improvement in gingival inflammation in smokers after a probiotic intervention using *Lactobacillus salivarius* [35]. Other studies have shown an improvement in gingival inflammation with probiotics, but no effect on the amount of plaque. This could be explained by a direct inhibitory effect of probiotics on competing inflammophilic periodontopathogens and/or a probiotic-induced downregulation of an excessive proinflammatory host response towards them [36,37].

Two recent systematic reviews addressing the effect of probiotics in improving or maintaining gingival health in orthodontic patients with fixed appliances have only identified 4 studies which were all focused on the short-term (1 month maximum) effect of probiotics [38,39]. In two studies, probiotics were not effective in reducing plaque (PI) and gingivitis scores (GI) [40,41], while in the other two PI and GI were improved in patients receiving probiotics [42,43]. Other studies have investigated the influence of probiotics on the composition of the oral microbiota, but the effect on the number of cariogenic or periodontal pathogens remains inconclusive [38,39]. Therefore, the therapeutic potential of oral probiotics in orthodontic patients is yet to be investigated in high-quality studies of longer durations of intervention and follow-up.

The aim of this study is to evaluate the effect of twice-daily administration of probiotics in addition to tooth brushing on gingival inflammation in adolescents with fixed orthodontic appliances.

## 2. Materials and Method

### 2.1. Research Hypothesis and Objectives

The gingival index (Loë Silness) [44] would be lower in adolescents with fixed orthodontic appliances receiving probiotics in addition to oral hygiene compared to those practicing oral hygiene alone.

#### 2.1.1. Primary Objective

Evaluation of the gingival index at 3 months: to compare the effect of twice-daily administration of probiotic lozenges during 3 months in addition to tooth brushing versus tooth brushing alone on gingival index at 3 months in adolescents undergoing treatment with fixed orthodontic appliances.

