#### 2.1.2. Secondary Objectives

To compare the effect of adjunctive probiotics on the following parameters:Gingival index at 6 months (i.e., 3 months after cessation of the lozenges intake).Extent and severity of gingivitis (at 3 and 6 months).Plaque accumulation on dental surfaces (at 3 and 6 months).Relative abundance of bacterial taxa at the phylum level in the supra and sub gingival microbiota (at 3 and 6 months).Level of salivary biomarkers of inflammation (at 3 and 6 months).

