### 2.4. Sample Size Calculation

The minimal sample size to assure adequate power for this study was calculated based on the variation of the mean gingival index at 6 months after treatment [45]. Considering a difference of 0.3 in the gingival index value at 6 months between the test and control groups, a significant level of 5% (two-sided test) and an attrition rate of 10%, 58 subjects should be included in each group to provide a power of 80%, i.e., a total of 116 patients.

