### 2.7. Primary and Secondary Outcomes Variables

The primary outcome is the difference for gingival index at 6 months post-treatment [46,47]. Secondary outcomes include:

Difference between baseline and 3–6 months post-therapy for bleeding on probing (BOP) [48];

Mean number and percentage of participants with different BOP thresholds (e.g., BOP < 30%, BOP ≥ 30%), and gingival index thresholds (e.g., GI ≤ 1, GI ≥ 2) 3 and 6 months post therapy;

Difference between baseline and 3–6 months post-therapy for plaque score [49];

Differences between groups in occurrence of adverse events, compliance [50], and patient-reported outcomes [50];

Difference in the relative abundance of bacterial taxa in subgingival microbiota (alpha and beta diversity, Bray–Curtis distance and UniFrac).

Levels of 20 cytokines and inflammatory mediators in saliva at 3 and 6 months after therapy.

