### 2.13. Statistical Analysis

All statistical analyses will be performed in an independent and blind way to the allocated group, using SAS software (SAS Institute, Cary, NC, USA). The level of significance will be set at 5%. The data will be evaluated using intention-to-treat analysis with the last observation carried forward. To ensure comparability between groups, the characteristics of the patients at inclusion will be described for each of the two study groups. Quantitative variables will be described by the mean and standard deviation in case of normality of the distribution, or by the median and interquartile range otherwise. The normality of the distributions will be confirmed by the Shapiro–Wilk test. The qualitative variables will be described by the numbers and percentages of each variable.

The variation of the gingival index (difference between baseline and 6-month measurement) will be estimated and compared between the two groups using a constrained longitudinal data analysis (cLDA) model as proposed by Liang and Zeger [54]. In this mixed linear model, the initial and post-treatment values will be coded as dependent variables, with a restriction on a value common to both groups at inclusion in order to control for the change between groups with respect to the baseline value and to take into account all available measures [55]. The mean change at 6 months between the groups (adjusted on baseline values) will be estimated by the time x group interaction term. In case of deviation from normality, the difference between the baseline and 6 month measures will be calculated and compared between groups using a non-parametric analysis of covariance adjusted on the baseline measure [56,57]. The variation between baseline and 3–6 months for BOP, plaque score, alpha/beta diversity index and levels of inflammatory mediators will be analyzed by the cLDA method described above for the primary outcome. A stepwise logistic regression analysis will be performed to investigate the impact of predictor variables on the clinical endpoint for treatment (e.g., BOP < 10%, GI ≤ 1). Descriptive analyses will be performed for the number of adverse effects, compliance and patient related outcomes.

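### The primary objective is the gingival index at 3 months, but the primary outcome, sample size and primary contrast are set at 6 months

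*Protocol article*

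**What the plan says.** The protocol article assigns the primary role to two different visits.

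**3 months.** Section 2.1.1 (Primary Objective): "Evaluation of the gingival index at 3 months: to compare the effect of twice-daily administration of probiotic lozenges during 3 months". Section 2.1.2 then lists as a secondary objective: "Gingival index at 6 months (i.e., 3 months after cessation of the lozenges intake".

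**6 months.**
- Section 2.7 (outcomes): "The primary outcome is the difference for gingival index at 6 months post-treatment".
- Section 2.4 (sample size): the calculation was "calculated based on the variation of the mean gingival index at 6 months after treatment", and the target is stated as "Considering a difference of 0.3 in the gingival index value at 6 months between the test and control groups".
- Section 2.13 (analysis): the constrained longitudinal model (cLDA) compares the change from baseline to 6 months. "The mean change at 6 months between the groups (adjusted on baseline values) will be estimated by the time x group interaction term". The non-parametric fallback uses the same 6-month change, and the section later refers to this method as the one for the primary outcome.

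Lozenges are taken for 90 days (section 2.6). The Discussion says that the 6-month visit is there to look for any effect that remains after they are stopped. The aim at the end of the Introduction gives no time point, so it does not settle the matter.

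**The concern.** The two visits answer different questions. At 3 months the contrast measures the effect at the end of intake. At 6 months it measures what is left about 3 months later. The same variable at the same visit is secondary in section 2.1.2 and primary in section 2.7.

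If the trial is run as sections 2.4, 2.7 and 2.13 say, its confirmatory test answers a stated secondary objective, and the stated primary objective has no effect size, power or named contrast. If one visit gives a significant difference and the other does not, a reader of this document could not say whether the trial met its primary aim. The text could be cited for either visit, so it offers no clear protection against a choice made after the results are known.

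**Working it through.** **1. The sections side by side**

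| Section | Time point for GI | Role |
|---|---|---|
| 2.1.1 | 3 months | primary objective |
| 2.1.2 | 6 months | secondary objective |
| 2.4 | 6 months | basis of the sample size |
| 2.7 | 6 months | primary outcome |
| 2.13, cLDA | 6 months | primary contrast |
| 2.13, fallback | 6 months | primary contrast if not normal |

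For GI at 3 months, section 2.7 lists only threshold counts (such as GI ≤ 1 and GI ≥ 2). The list in section 2.13 of variables analysed over 3–6 months covers bleeding on probing, plaque score, diversity indices and mediators, but not mean GI. The cLDA is meant to use all available measures, so the 3-month value can enter the model, but no 3-month contrast is named.

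**2. The plan's own sample size**

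Inputs from section 2.4: difference 0.3 at 6 months, two-sided 5%, 80% power, 10% attrition. The stated result is "58 subjects should be included in each group to provide a power of 80%, i.e., a total of 116 patients". The section gives no standard deviation (SD), so the figure cannot be reproduced directly. Solving back:

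- Evaluable per arm: 58 × 0.90 = 52.2, taken as 52.
- Normal approximation: SD = 0.3 / [(1.960 + 0.842) × √(2/52)] = 0.546.
- t-test with 52 per arm: the detectable standardised difference is 0.555, so SD = 0.3 / 0.555 = 0.541.

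The stated size is consistent with an SD of about 0.54 to 0.55 at 6 months. This SD is inferred, not stated.

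**3. Does the sizing carry over to 3 months?**

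Power ≈ Φ(δ / [SD × √(2/52)] − 1.96), for an unadjusted comparison. The 3-month values below are assumptions.

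- SD 0.54, difference 0.20 / 0.25 / 0.30 / 0.35: power 47% / 66% / 81% / 91%.
- Difference 0.30, SD 0.45 / 0.50 / 0.60 / 0.65: power 92% / 86% / 72% / 65%.

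The 80% holds at 3 months only if both the 0.3 and the SD hold there, and section 2.4 speaks only of 6 months.

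**4. Type I error if the visit were chosen after the results**

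P(|Z₁| > 1.96 or |Z₂| > 1.96) under the null, bivariate normal with correlation ρ between the two test statistics (ρ is assumed):

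| ρ | Two-sided error |
|---|---|
| 0 | 9.75% |
| 0.3 | 9.5% |
| 0.5 | 9.1% |
| 0.7 | 8.3% |
| 0.9 | 7.0% |

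**The case against.** The strongest reply is that the operative parts agree. The named outcome, the sizing, the model contrast and the fallback all say 6 months, so a confirmatory test is pre-specified and only the objectives disagree with it. Section 2.13 also has the analysis done blind to allocated group. This stands as far as it goes. A reader might infer two co-primary endpoints with an inflated error rate, but the document declares none and gives no permission to choose between visits. It does not remove the contradiction: an unseen analysis plan could follow only one designation, and the other published statement would then be wrong.

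Three further readings are tempting and are not supported:

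- *That GI at 3 months is not analysed at all.* Section 2.7 lists GI thresholds at that visit, and the model can use the 3-month value. What is absent is a named mean-GI contrast.
- *That the wording of sections 2.4 and 2.7, which counts from treatment, means a visit near month 9.* Section 2.1.2, the Discussion and Table 1 fix the last visit at 6 months. This is a matter of wording only.
- *That a probiotic whose effect wanes would certainly be declared negative.* The document gives no waning effect. Section 2.4 places the 0.3 at 6 months itself, and the baseline-constrained model may be more efficient than the unadjusted comparison used above.

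**Conclusion.** The concern holds as an internal contradiction over one primary endpoint. It is in the current text, each side is stated in more than one place, and nothing reconciles them. It should be corrected before unblinding, because the primary time point determines the hypothesis tested, the meaning of the sample size and the trial's conclusion.

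The contradiction itself rests on no assumption. The figures do. The 8.3% to 9.5% applies only if the visit is picked after results are seen, with correlations of 0.7 to 0.3; it is not the error rate of the analysis in section 2.13. The 3-month power values rest on an SD solved back from the stated sample size, or on other assumed SDs, and on assumed differences. They show that the sizing cannot simply be relabelled, not that the trial is underpowered.

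**What to change.** Before unblinding, fix one primary time point and use it in sections 2.1.1, 2.1.2, 2.4, 2.7 and 2.13. There are two coherent options.

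**(a) 3 months primary.** Take the 3-month group contrast from the cLDA as primary. Test the 6-month contrast from the same model second, only if the first is significant, each at 5% two-sided; this fixed sequence keeps the overall error at 5%. In section 2.4, justify that the 0.3 difference and its SD apply at 3 months, or restate the power. This costs a protocol amendment and a new sizing argument, not only a change of wording.

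**(b) 6 months primary.** Leave the sizing, outcome and model as they are. Rewrite sections 2.1.1 and 2.1.2 so that the primary question is the residual effect after intake ends, and name the 3-month mean-GI contrast from the same model as key secondary. This costs an amendment to wording only.

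Under either option GI is already examined at both visits (section 2.9 and Table 1), so no visits are added. Patients would be added only if the power restated under (a) were judged too low. As a wording note, give all time points as months after baseline.

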#### 2.1.2. Secondary Objectives

To compare the effect of adjunctive probiotics on the following parameters:Gingival index at 6 months (i.e., 3 months after cessation of the lozenges intake).Extent and severity of gingivitis (at 3 and 6 months).Plaque accumulation on dental surfaces (at 3 and 6 months).Relative abundance of bacterial taxa at the phylum level in the supra and sub gingival microbiota (at 3 and 6 months).Level of salivary biomarkers of inflammation (at 3 and 6 months).

### 2.2. Study Design

The present study is a single-center, randomized, double blinded, two-armed, placebo-controlled trial conducted at Lille University-Hospital (CHU Lille, France). The study protocol was developed according to the Standard Protocol Items Recommendations for Interventional Studies (SPIRIT) and registered in the ClinicalTrials.gov (accessed on 16 December 2021) (NCT04634201) database.

### 2.3. Ethical Considerations

This trial will be conducted in accordance with the principles of the Declaration of Helsinki for studies involving humans. The protocol has been approved by the Institutional Review Board of OUEST IV (France)—CPP 1360 HPS2 (N° RIPH: 20.11.20.40523). All eligible volunteers will be informed (orally and written) about the nature, potential risks, and benefits of their participation in this study, and they will sign an informed consent.

### 2.4. Sample Size Calculation

The minimal sample size to assure adequate power for this study was calculated based on the variation of the mean gingival index at 6 months after treatment [45]. Considering a difference of 0.3 in the gingival index value at 6 months between the test and control groups, a significant level of 5% (two-sided test) and an attrition rate of 10%, 58 subjects should be included in each group to provide a power of 80%, i.e., a total of 116 patients.

### 2.5. Subject Population and Inclusion/Exclusion Criteria

Volunteers will be recruited from the outpatients of the orthodontics clinic of the University Hospital of Lille, France. Subjects will be selected according to the following criteria: (i) adolescents aged between 12–16 years, (ii) in good systemic health and proficient in tooth brushing, (iii) eligible for full arch upper and lower fixed labial orthodontic appliance treatment, (iv) with no active untreated periodontitis or evolutive gingival recession; (v) willing and able to comply with the study protocol and whose parents/guardians have given their consent. Exclusion criteria include (vi) inability to obtain informed consent, the presence of (vii) allergies, sensitivities or food intolerance to any of the components of the probiotic lozenges or placebo, (viii) systemic diseases that could affect the periodontal status (e.g., diabetes, immunological disorders), (ix) chronic use of probiotics or food supplements, and (x) use of antibiotic therapy in the previous month/ need for antibiotic premedication for dental treatment and long-term intake of anti-inflammatory drugs.

### 2.6. Interventions

At baseline, demographic, oral and general health information will be collected. Subsequently, a clinical periodontal examination, as well as supra and sub gingival biofilm and saliva sampling will be performed. A professional mechanical plaque removal will be provided using air-polishing combined with manual and ultrasonic scalers and patients will receive oral hygiene instruction (OHI), including tooth brushing and inter-proximal dental hygiene using interdental brushes. Subsequently, patients will be randomly allocated to one of the following groups: (i) control: two placebo lozenges a day for 90 days together with regular oral hygiene, (ii) test: two probiotic lozenges a day for 90 days together with regular oral hygiene (Figure 1 and Table 1). The administration of probiotics and placebo will start on the day of placement of fixed orthodontic appliances. The probiotic (or placebo) will be delivered for 4 weeks and will be refilled periodically. The probiotic studied (Gum^®^ PerioBalance^®^) is commercially available in France. Probiotic and placebo are prepared by Bio-Gaia AB (Stockholm, Sweden). Each lozenge of probiotic contains two strains of probiotic lactic acid bacteria of human origin: *L. reuteri* DSM 17938 and *L. reuteri* ATCC (PTA 5289), each at a minimum amount of 1 × 10^8^ CFU per lozenge. The probiotic will be used according to the manufacturer’s recommendations at a dosage of 2 lozenges/day. The composition and packaging of the placebo will be identical in all aspects to the probiotic but do not contain *L. reuteri*. The lozenges should be stored at a temperature below 25 °C. Patients will be asked to avoid the concomitant use of antibiotics or antiseptic mouthwashes. However, if the use of these medications is required by prescription, the principal investigator should be informed.

